## Abstract

The high prevalence rate and ever-increasing incidence of tuberculosis (TB) worldwide remain a significant issue in healthcare. In Malaysia, the incidence and mortality rate of TB is increasing due to the delayed presentation of TB patients to healthcare facilities. However, there is a lack of local studies on the contributing factors of delayed presentation of TB patients in Malaysia. This study aims to establish a social epidemiology framework by analysing social factors including socio-epidemiological, socio-cultural, and health-seeking behaviours associated with the delay in seeking TB treatment among patients in Selangor, Malaysia. A sequential exploratory mixed-method study design that combines qualitative and quantitative research methods will be employed. This study will recruit adult patients who have been diagnosed with TB using chest X-ray and sputum smear microscopy. Four districts with the highest recorded cases in the state of Selangor will be selected as study locations. The qualitative study will involve a Focus Group Discussion (FGD) to explore six components, namely demographic, socio-cultural, health-seeking behaviours, social support and resources, previous knowledge and experience with illness, and treatment pathway. Meanwhile, the quantitative study will incorporate a structured survey that will be developed based on the themes identified in the qualitative phase and a review of several studies in the literature. Several quality control measures will be taken while ensuring that the survey questionnaires are anonymised and participants’ confidentiality is maintained. The data obtained from both qualitative and quantitative approaches will be combined to provide a more robust assessment of the study. Given that this study will focus on districts with high recorded cases of TB in Selangor, the findings might assist to address TB-related issues such as the increasing incidence and mortality rates, which are mainly attributed to the delayed presentation of TB patients to healthcare facilities.

## Introduction

Tuberculosis (TB) is an airborne communicable disease caused by Mycobacterium tuberculosis (MTB), an anaerobic pathogenic bacillus [1, 2]. It is recognised as one of the infectious diseases with a high mortality rate that spreads through airborne transmission. About one-fourth of the world’s population is estimated to be infected with MTB [3]. Although the vast majority are non-infectious and asymptomatic, they are still at risk of developing active TB disease and becoming infectious. The manifestations of TB disease differ among the population, some patients develop symptoms within weeks of being infected before their immune system can fight the bacteria, whereas some may fall sick only years later when their immune system becomes weakened for other reasons [4].

As an airborne disease, TB spreads through infectious droplets known as droplet nuclei that can be easily transmitted to other hosts or remain in the air for several hours, depending on the surrounding environment [4, 5]. The transmission usually occurs when an individual inhales the droplet nuclei and the bacterium attacks the lungs. Additionally, the infection can affect other organs such as the kidney, brain, and spine. Common TB symptoms include chest pains, loss of appetite, loss of weight, fatigue, fever, muscle and joint weakness. The patients also suffer from prolonged cough for more than 3 weeks, with or without haemoptysis [4, 5].

Due to the high incidence of TB, many developed and developing countries worldwide are facing a heavy healthcare burden in managing this disease, including India, Indonesia, and Nigeria [6]. Based on the STOP TB strategy by The World Health Organisation (WHO), the global prevalence and mortality rate of TB by 2015 should reduce by 50% compared to that reported in 1990 [4]. In 2019, an estimated 10 million cases, or equivalent to 133 cases per 100,000 populations of TB was reported globally [7]. Moreover, in 2019, the number of new cases of TB globally was 7.1 million, an increase from 7 million in 2018 and 6.4 million in 2017, as well as a marked increase of 5.7 to 5.8 million annually between 2009 and 2012 [2, 7, 8]. Out of the new cases in 2019, 62% were reported in Southeast Asia (SEA) and the Western Pacific areas, followed by 25% in the African region. In the SEA, the incidence of TB was 226 cases per 100,000 population [9]. Concurrently, the number of TB-related death was 2.8 per 100,000 populations, with the highest incidence recorded in the Philippines (555 cases per 100,000 population) and the lowest in Malaysia (93 cases per 100,000 population) (WHO, 2018).

TB accounts for the second-highest mortality from a single infectious agent after HIV/AIDS. The aetiology of TB is complex. The risk of contracting TB is higher among people with existing health conditions, especially among patients with Human Immunodeficiency Virus (HIV). Specifically, they are 30 times at higher risk of developing TB than those without HIV [10]. Furthermore, TB is classified as the leading cause of death among HIV patients due to the increased risk for inflammatory immune reconstitution (IRIS) [10]. In 2017, 9% of TB cases were detected among persons with HIV infection [2]. Besides, people with underlying diabetes mellitus are also at a higher risk of developing TB. A recent study reported that diabetic patients are three times more likely to develop TB [11]. The incidence of TB patients with diabetes mellitus is particularly high in the low- and middle-income countries (LMIC). In addition, another study found that men with adenocarcinoma as well as women with asthma or early-stage adenocarcinoma suffered from an increased risk of TB-related mortality [12].

Apart from existing medical conditions, socio-economic and cultural factors are also the determinants of TB infection. Poor economic status can limit the economic resources of individuals, causing them to live in an overcrowded housing area with a cheaper rental rate. Past evidence highlighted that an overcrowded living condition can predispose to an increased risk of developing TB among the dwellers [13]. In addition, poor economic status also reflects a lower education level that impedes the understanding of TB, especially in terms of the transmission process and symptoms of TB. Previously published studies have stressed the importance of reducing education inequalities to bring down the incidence of TB [14, 15].

In addition, TB is commonly known as the barometer of social welfare. In other words, the prevalence is a reflection of the effectiveness of the social welfare programme offered by the government to the citizens. A high number of TB cases in certain populations may indicate poor urban planning and healthcare provision by the government [16]. Other social factors associated with TB infection include quality of life, population growth, malnutrition, lifestyle habits such as smoking and alcohol consumption, overcrowded family homes, early marriages, poor knowledge, and lack of awareness on the cause and transmission of TB [17]. These factors are also correlated in the occurrence and transmission of TB.

The increasing trend of global TB infection in recent years could also be attributed partly to the improved diagnostic method of the disease. Detection of the infectious status and the stage of disease in TB patients is crucial as it influences the prognosis and treatment outcomes of TB cure. Delayed presentation of TB is associated with a higher failure rate of treatment and death [18]. Moreover, in clinical practice, the diagnosis of TB can be challenging as it closely mimics the symptoms of pneumonia. Very often, patients are treated as pneumonia and prescribed antibiotics before TB is officially diagnosed [18]. On a similar note, it is also difficult to diagnose individuals with TB/HIV co-infection [19]. Many of the current diagnostic techniques lack precision in detecting positive cases. They can also be time-consuming, costly, or require advanced laboratory equipment that is limited in developing countries [19].

The TB diagnostic tools endorsed by WHO can be divided into traditional tools such as symptom screening, chest x-ray, microscopy staining, or newer tools such as Interferon-gamma Release Assay (IGRA), Fluorescent Staining (LED), Liquid Media Culture, and Polymerase Chain Reaction [20]. The newer tools significantly improve the case detection rate, based on the declining mortality rate by 42% and a higher rate of treatment success (82%) among newly diagnosed cases between 2000 and 2017 [2]. Sputum is the gold standard for TB diagnosis. However, some difficulties in obtaining the sputum samples have been reported, especially among children and HIV-infected individuals [19].

Diagnosing and treating TB at a late stage may negatively impact the effectiveness of the treatment plan. Therefore, it is imperative to address factors that contribute to the delayed presentation among TB patients, such as social factors, lack of awareness and knowledge of TB, healthcare provider-related barriers, and belief in traditional treatment.

### Why is it important to conduct this study?

In recent years, the incidence and mortality rates of TB is increasing rapidly in Malaysia with the influx of immigrants. A high incidence of TB can negatively impact the country’s social development and offset the economic growth in various aspects. To reduce the incidence of TB and its mortality rate, suspected patients must be diagnosed at the earliest stage. However, due to a lack of knowledge and awareness of TB as well as limited healthcare facilities, patients with TB are often diagnosed late.

In Malaysia, Selangor recorded a total of 375 deaths and the highest number of TB cases in 2018 (5,071 cases), contributing to almost 18% of the overall cases in the country [21]. Selangor is the most populated state in Malaysia with a population of more than 6.4 million. It comprises nine districts and the four bigger districts namely Hulu Langat, Gombak, Petaling, and Klang accounted for the highest percentages of TB cases in Selangor [21]. Currently, there is a lack of evidence on the contributing factors of delayed treatment among TB patients. Therefore, this protocol outlines a study that is planned to explore the reasons behind the delay in seeking TB treatment among TB patients in Malaysia.

## Objectives

To develop a framework by analysing the social factors associated with delay in seeking treatment among TB patients in Selangor. This study will describe the socio-epidemiological characteristics (socio-demographic and socio-cultural) of TB patients in Selangor, Malaysia. This study will determine the common barriers faced by health providers in Selangor and the association between patients’ health-seeking behaviour and their social epidemiological factors (socio-demographics and socio-cultural), as well as health provider barriers. Finally, this study protocol aims to construct a predictive social epidemiology framework to identify contributing factors towards the delay in seeking treatment among TB patients in Selangor, Malaysia.

## Research questions

Due to the high incidence of TB infections in the state of Selangor, the research aims to answer the following questions:

What is the incidence rate of TB in Selangor?What is the distribution of socio-demographic factors among the TB patients in Selangor?What is the distribution of socio-cultural factors among the TB patients in Selangor?What is the distribution of health-seeking behaviours among the TB patients in Selangor?What are the barriers faced by healthcare providers that can influence the TB diagnosis?How do the socio-demographic, socio-cultural, and health provider factors interact to influence health-seeking behaviours among TB patients?

To answer the aforementioned research questions, this research focuses on the identification of risk factors for delayed presentation of TB in Selangor.

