## Methods

### Study design and study area

This study will adopt a mixed-method research design. We will combine quantitative and qualitative approaches to obtain comprehensive results regarding the research questions [22]. The exploratory sequential mixed methods design will be conducted for the data collection. Data collection will be performed among patients who have been diagnosed with TB using chest X-ray and sputum smear microscopy. Four districts with the highest recorded cases in the state of Selangor will be selected as study locations. The sampling frame will be determined from the MyTB system database and patients fulfilling the inclusion criteria will be identified as sampling units. Thereafter, they will be categorised based on the four districts to ensure there are respondents from each district.

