### Study population

The study population will comprise TB patients in the state of Selangor.

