### Qualitative phase: Study instrument and focus group discussion

Upon identifying the samples for the quantitative study, a subsample will be selected among them to participate in the Focus Group Discussion (FGD). As a rule of thumb, 10% of the estimated sample size for the quantitative study will be selected to join the FGD. Meanwhile, the number of participants participating in the FGD will be equally distributed across the four districts. A semi-structured questionnaire will be used for the FGD respondents to share their thoughts and opinions. The qualitative study aims at identifying and better understanding the social factors related to their delayed presentation to the healthcare centres.

Six components will be explored during the discussion, namely demographic, socio-cultural, and health-seeking behaviours, social support and resources, previous knowledge and experience with illness, as well as treatment pathway. The guide will be revised in subsequent FGD to probe any new emerging themes. In all the FGDs, the discussions will be audio-recorded and transcribed verbatim after that. The concept of theoretical saturation will be used to ensure no new conceptual information emerges from the discussion. Subsequently, all the findings from the qualitative phase will be transcribed and coded. The identification, coding, and categorisation of meaningful patterns into themes and subthemes will be conducted to facilitate the construction of a structured questionnaire for the quantitative study. Interview transcripts will be analysed using NVivo (Version 12).

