**Fig 1 pone.0266746.g001:**
[figure not shown]
Research design of the different study phases.

**Table 1 pone.0266746.t001:** Research matrix.

RESEARCH OBJECTIVES	QUANTITATIVE	QUALITATIVE
To describe the incidence of TB in Selangor and the health-seeking behaviour (timeline between the onset of symptoms to the first presentation to the healthcare facility and medical visit) among the patients.	√	√
To describe the social epidemiological characteristics (socio-demographic and socio-cultural) of the TB patients in Selangor.	√	
To determine the types of health provider barriers that are prevalent in Selangor.	√	√
To determine the association between health-seeking behaviour and social epidemiological factors (socio-demographics and socio-cultural) as well as health provider barriers.	√	
To investigate the key factors that contribute to delayed presentation of TB patients.		√
To construct a predictive social epidemiology framework for the identification of delay in seeking treatment among TB patients in Selangor.	√	√

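### Barriers faced by health providers are an objective, but every stated respondent is a patient and the only stated interval stops before diagnosis, so at most patient-perceived barriers can be measured

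*Protocol article*

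**What the plan says.** Three places in the protocol article commit the study to provider barriers.

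- Objectives: "This study will determine the common barriers faced by health providers in Selangor". The same sentence adds their association with patients' health-seeking behaviour.
- Research questions, fifth: "What are the barriers faced by healthcare providers that can influence the TB diagnosis". Sixth: "How do the socio-demographic, socio-cultural, and health provider factors interact to influence health-seeking behaviours among TB patients".
- Table 1, row 3: "To determine the types of health provider barriers that are prevalent in Selangor", ticked for both the quantitative and the qualitative phase. Row 4, on the association with health-seeking behaviour, is ticked for the quantitative phase only. Row 6, the predictive framework, is ticked for both.

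On who supplies data, Study design and study area says: "Data collection will be performed among patients who have been diagnosed with TB using chest X-ray and sputum smear microscopy". Study population says: "The study population will comprise TB patients in the state of Selangor".

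On what is asked in the focus groups: "Six components will be explored during the discussion, namely demographic, socio-cultural, and health-seeking behaviours, social support and resources". The remaining two components are prior knowledge and experience of illness, and the treatment pathway.

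On timing, Table 1 row 1 describes health-seeking behaviour as the "timeline between the onset of symptoms to the first presentation to the healthcare facility and medical visit".

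**The concern.** A barrier that a provider faces in diagnosing TB is a fact about the provider's working conditions: the tests at hand, their precision, confusion with other disease. A patient sees part of this from outside and cannot report the rest. If only patients are asked, their perceptions may be published as providers' barriers, or the objective may go unanswered.

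There is also a question of order in time. The fifth question concerns barriers that bear on diagnosis, whereas the timed behaviour ends at presentation. If diagnostic-stage barriers were related to that interval, the supposed cause would follow its effect, and the association could pass into the framework that Table 1 row 6 calls predictive.

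**Working it through.** No arithmetic applies. The protocol gives no figure on this point, so the check sets its sections side by side.

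**1. Who responds**

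| Section | Role | Who |
|---|---|---|
| Study design and study area | Sampling units, from the MyTB database | Patients |
| Study population; Inclusion criteria | Eligible persons | Confirmed TB patients |
| Qualitative phase | Focus group members | Subsample of the same patients |
| Quantitative phase | Survey recipients | Patients selected by the sampling scheme |
| Ethical consideration | Participants | Adults with TB |
| Quantitative phase | Content validity | Three field experts |
| Quantitative phase | Face validity | Ten healthcare professionals |
| Quantitative phase | Building the framework | Expert panel |

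The last three rows are reviewers or advisers, not respondents. Facilities are also selected (Sample size calculation and sampling technique), but only as places from which patients are drawn. Number of providers stated as respondents in either phase: 0.

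**2. What is asked**

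None of the six focus group components is named for provider barriers; the treatment pathway is the nearest. The questionnaire will be built from focus group themes and a literature review, so provider items may still enter. However, Data analysis lists the variables to be summarised as socio-demographic characteristics, socio-cultural factors, health-seeking behaviours and delayed presentation. Provider barriers are not among them.

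**3. Which interval is timed**

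Table 1 times health-seeking behaviour from symptom onset to first presentation and medical visit. Data analysis names delayed presentation, in days and weeks, with no start or end point. The reference to a medical visit may extend the interval to the first consultation, but it still stops short of diagnosis. The mention of treatment delays in the sample size section concerns only the studies from which P1 and P2 will be taken. Number of defined intervals from presentation to diagnosis or treatment start: 0.

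**4. Which barriers can act on that interval**

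- *Before presentation.* Poor access or a shortage of facilities can hold a patient back from a first visit. The section on why the study is important mentions the latter, and the Introduction counts provider-related barriers among the contributors to late presentation. These can be related to the Table 1 interval.
- *During diagnosis.* The Introduction describes patients first treated for pneumonia, and tests that lack precision or need scarce equipment. The patient has by then already presented, so these barriers cannot have lengthened the time to first presentation.

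**5. Extent**

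The fifth of six research questions is affected as worded, and the sixth in part. Table 1 rows 3 and 4 depend on it directly; row 6 depends on it through one input among several.

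**The case against.** The best defence is that only the words about barriers faced by providers point to the providers' own view. Table 1 row 3 speaks of types of health provider barriers and the sixth question of health provider factors; both can be read as obstacles that patients meet and can report. The treatment pathway component could elicit them, the focus group guide may be revised as themes emerge, and the questionnaire does not yet exist. Fig 1, which is said to set out the design by research question, is not available here.

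Much of this stands. It rules out the reading that the question is wholly unanswerable: patients can supply perceived barriers, and the literature review may add items. It does not supply providers' own barriers, because the population and sampling sections name patients alone. Fig 1 might show another source, but that would conflict with the text.

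A reader might also infer that the plan puts exposure after outcome throughout, in a regression of patient delay on provider barriers. The article does not support that. The interval is Table 1's gloss on health-seeking behaviour, not a formal outcome definition. Data analysis names no covariates for the regression. The association objective is not confined to diagnostic-stage barriers. The problem of order holds only for barriers that arise during diagnosis.

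Finally, rewording alone would remove the contradiction about respondents, and a second interval widens a study focused on late presentation. That is fair, but without the second interval there is no stated outcome to which a barrier to diagnosis can properly be related.

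**Conclusion.** The concern holds in a limited form. The objectives promise barriers faced by providers that bear on diagnosis, while the stated design can yield at most patients' perceptions of provider or access barriers. This is a conflict between sections of the article, not a detail left to a fuller document. Diagnostic-stage barriers cannot explain delay before first presentation; barriers acting earlier can.

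This should be fixed but is not critical, because the lead aim, patients' social factors and delay in seeking treatment, does not depend on it. The conclusion assumes that the stated respondents are the complete list, and that the medical visit in Table 1 means no later than the first consultation.

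**What to change.** 1. Reword the objective, the fifth and sixth research questions and the affected Table 1 rows as patient-reported health-system and access barriers.
2. Include items on these barriers in the survey questionnaire before it is fielded. According to the Timeline, recruitment for the qualitative phase is complete and survey recruitment starts in March 2022, so the survey is the practical place for the repair.
3. Record the date of diagnosis or treatment start, giving two intervals: symptom onset to first presentation, and first presentation to diagnosis or treatment start.
4. Relate pre-presentation access barriers to the first interval only, and diagnostic-stage barriers to the second only, and carry that separation into the framework.

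The cost is some rewording, a few questionnaire items and one date. The drawback is a narrower claim about providers. A provider sample is needed only if the sponsor wishes to keep the objective as now worded. The change should come before fielding, since items and dates missed in a single cross-sectional survey may be hard to recover and analysis cannot replace them.
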